## **1. BACKGROUND/RATIONALE/PRESENT STATE OF KNOWLEDGE**

### **1.1. Overall Aim:**

About one to three percent of adults in Canada have an intellectual and developmental disability (IDD), and 20-40% of them have severe behavioural problems (SBP), including self-injurious behaviour, disruptive behaviour, or aggression. SBP are common contributors to morbidity and reduced quality of life for adults with IDD and their families. Current medications for SBP show equivocal effectiveness and are associated with a high risk of side effects. Innovative and safe treatments are urgently needed to increase quality of life and reduce morbidity, caregiver burden, and health care costs. While preclinical studies, anecdotal reports, and uncontrolled studies link SBP with an endocannabinoid mechanism and suggest that medical cannabinoids may be an efficacious and safe alternative to current medications for SBP in adults with IDD, rigorous evidence is still in the very early stages. Unlike cannabidiol (CBD), a cannabinoid with elusive mechanisms and dose ranges, nabilone, a marketed synthetic cannabinoid, has a clearer mechanism, favourable safety profile, and more predictable dosing. Data of safety and efficacy regarding nabilone in this population has never been published. Parallely, evaluating the effects of nabilone using MRI (especially fMRI and H MRS, which measure brain function and metabolism, respectively) optionally in some participants has the potential to reveal mechanisms underpinning behavioural changes post-treatment, thereby facilitating the development of better designs in using cannabinoid for SBP in IDD. Thus, we propose to conduct this investigator-initiated Phase I pre-pilot open-label clinical trial.

**Primary Aim 1:** To collect preliminary data on the tolerability and safety profile of nabilone in adults with IDD.

**Hypothesis 1:** To evaluate tolerability, we hypothesize that 80% of participants will complete the study protocol.

**Hypothesis 2:** To evaluate safety, we hypothesize that nabilone will be satisfactorily tolerated and have a favourable safety profile in adults with IDD, as quantified by lower rates of adverse events (AEs) and serious adverse events (SAEs) than those reported in the literature of antipsychotics in IDD.

**Exploratory Aim 2:** We will explore changes in SBP, as well as brain changes on MRI, which is optional, in participants pre-and post-treatment.

The trial includes a screening visit for eligibility, a baseline visit followed by a dose titration phase, and then a 4-week open label phase at a stable dose. At the end of the open label phase, participants will undergo a termination visit, after which nabilone will be tapered off over 8 days. And then, 2 weeks later, participants will undergo a last follow-up visit to ensure safety.

Findings from this project will inform the design of a series of follow-up clinical trials, i.e., a next-stage Phase I/II pilot placebo-controlled randomized controlled trial (RCT) to test the feasibility of a larger trial, followed by a Phase II/III multicentre RCT. This planned Phase I study and the ensuing trials will address an evidence-practice gap in the use of cannabinoid to meet a pressing need for services, community and families.

### **1.2. The Need for More Research to Develop Innovative Treatment for SBP in Adults with IDD:**

About 1-3% of adults in Canada have an intellectual and developmental disability (IDD) (1), and 20-40% of them have severe behavioural problems (SBP), including self-injurious behaviour, disruptive behaviour, or aggression (2), in the absence of a confirmed psychiatric diagnosis. These SBP are associated with emotion dysregulation, pain, and sleep problems (3). SBP are major contributors to morbidity, functional impairments, missed opportunities for learning, reduced quality of life, and burden on families, health, education and disability sectors (4).

SBP in adults with IDD are extremely difficult to treat. Although psychosocial interventions are generally considered first-line treatments per national and international guidance (5, 6), for a subgroup of people with IDD and SBP, these options are not effective. Antipsychotics and other psychotropic medications are thus prescribed for up to 70% of adults with IDD (7, 8), off-label, and with equivocal efficacy (9). Further, people with IDD, relative to those without IDD, are at a higher risk of side effects of psychotropic agents and less able to report side effects (10, 11). These side effects include weight gain, metabolic disturbances, neurological symptoms, and avoidable death (12). Finally, because of suboptimal responses to currently available medications, polypharmacy is commonly used to treat SBP in adults with IDD (8), potentially leading to more adverse events (9). Thus, innovative and safer interventions are pressingly needed for this population.

### **1.3. Endocannabinoid System and SBP**

Stimulated by  $\Delta^9$ -tetrahydrocannabinol (THC), the primary psychoactive ingredient in cannabis, cannabinoid receptors 1 (CB1) of the endocannabinoid system modulate the activity of serotonergic, noradrenergic, dopaminergic, GABAergic, and glutamatergic neurotransmitters and is a potent modulator of myriads of cognitive and behavioural processes including learning and attention, emotion regulation, sleep structure, and pain perception (13). Cannabinoid receptors 2 (CB2), also activated by THC, are mainly localized in peripheral immune cells and are expressed in the brain during neuroinflammation. Inflammatory processes alter the metabolism and functions of neurotransmitters, neuroendocrine activity and neural plasticity, leading to the development of neuropsychiatric symptoms (14). Pro-inflammatory markers are positively linked with aggression in children with Prader-Willi Syndrome (60% of them have IDD and those without IDD have some learning disabilities) (15). Neuroinflammation is modulated by CB2 agonist (16).

CB1/2 agonists have also been tested in preclinical studies and, at lower doses, have been shown to reduce aggression. Further, CB1/2 knockout mice show more aggression than wild mice (17, 18). A theoretical review also suggest CB1 modulation may be a future candidate for treatment of self-injury (19).

Human functional MRI (fMRI) data suggest that at low doses, THC attenuates anxiety responses and also reduces amygdala reactivity and its functional coupling with frontal regions while processing stimuli with a negative emotional content. Conversely, at higher doses, the effect of acute administration of THC becomes anxiogenic (20). Parallely, human proton magnetic resonance spectroscopy ( $^1\text{H}$  MRS) studies indicate that the GABA and glutamate–glutamine balance, which is modulated by CB1, links with emotion regulation and related psychopathology (21).

### **1.4. Rationale for the Use of Nabilone in People with IDD and SBP**

Anecdotal reports (22) and preliminary research (23) suggest that medicinal cannabinoid may be useful to treat SBP in youth with developmental disabilities. However, and despite high hopes

held by families, the scientific evidence is in very early stages. Most studies to date focused on cannabidiol (CBD), as THC use is associated with cognitive decrements, psychotic symptoms, and addictive in recreational marijuana users (24). However, the full mechanism and dose range of CBD, which has very low affinity for CB1/2, remains elusive. Prior evidence suggests limited beneficial properties of CBD for aggression and risk factors associated with SBP (25).

Nabilone is a synthetic oral THC analogue that acts as a partial agonist on both CB1/2 in humans. Thus, it mimics the effect of THC on aggression/emotion regulation, sleep, and pain, but with more predictable side effects, better safety profiles, and less euphoria (26). Clinical studies suggest that nabilone may be useful in alleviating agitation in dementia (27, 28), nightmares in post-traumatic stress disorder (PTSD) (29), non-motor symptoms (mood dysregulation, sleep, pain) in Parkinson's disease (30), and core symptoms in anxiety and pain disorders (29). Preliminary studies suggest that another synthetic THC, dronabinol (a full agonist at CB 1/2), may be effective in alleviating SBP in youth with IDD (31, 32). However, dronabinol has been withdrawn from the Canadian market for unknown reasons. Moreover, nabilone, relative to dronabinol, has better bioavailability (33), may have less adverse mental effects (because of partial vs. full agonist properties), and may be more effective in alleviating SBP (27).

*Safety:* Nabilone is indicated for severe nausea and vomiting associated with cancer chemotherapy and is commercially available in Canada. Its use is usually safe and satisfactorily tolerated. The most frequently reported adverse reactions to nabilone in previous clinical trials are as follows: drowsiness (66.0%), vertigo (58.8%), psychological high (38.8%), dry mouth (21.6%), depression (14.0%), ataxia (12.8%), blurred vision (12.8%), sensation disturbance (12.4%), anorexia (7.6%), asthenia (7.6%), headache (7.2%), orthostatic hypotension (5.2%), euphoria (4.0%) and hallucinations (2.0%) (26-28, 30, 34, 35). The safety profile and rate of AEs for nabilone are comparable to those reported in studies of CBD (36) and clonidine (37), and substantially more favourable than what has been reported for antipsychotics (9, 11, 12).

The addictive potential of nabilone is very low and unlikely (38), because it is associated with less euphoria, slower onset of action, and more difficult titration compared to smoking cannabis. Nabilone has been shown to help with sustained abstinence of marijuana (39). The incidence of nabilone-induced psychotic symptoms is rare, and was only reported in people with personal/family history of psychosis.

Taken together, the evidence suggests that nabilone is a promising treatment for SBP in adults with IDD. However, the efficacy and safety of nabilone in this population have yet to be studied.

Evaluating the effects of this novel nabilone intervention using MRI, especially fMRI and H MRS, which measure brain function and metabolism, respectively, has the potential to reveal mechanisms underpinning behavioural changes post-treatment. This pharmacoinaging approach also enables the better understanding of response heterogeneity, thereby facilitating the development of better designs in using cannabinoid for SBP in IDD.

## **2. STUDY OBJECTIVES**

To address the current state of evidence for nabilone use to treat SBP in adults with IDD, we propose to conduct the first Phase I pre-pilot open-label clinical trial with the following aims and hypotheses:

**Primary Objective:** To collect preliminary data on the tolerability and safety profile of nabilone in adults with IDD.

Hypothesis 1: To evaluate tolerability, we hypothesize that 80% of participants will complete the study protocol.

Hypothesis 2: To evaluate safety, we hypothesize that nabilone will be satisfactorily tolerated and have a favourable safety profile in adults with IDD, as quantified by lower rates of AEs than those reported in the literature of antipsychotics in IDD.

**Exploratory Objective:** We will explore changes in SBP, as well as brain changes on MRI, which is optional, in participants pre- and post-treatment.

Significance/Innovation:

This is the first study to investigate nabilone for SBP in people with IDD. We will conduct a Phase I open-label trial to assess nabilone safety in this population, but with a fixed dosage range since it is an already marketed product (40). Findings from this project will inform the design of a series of clinical trials led by the PI in the future, i.e., a next-stage Phase I/II pilot placebo-controlled RCT to test the feasibility of a large-scale RCT, followed by a Phase II/III multicentre RCT to test available options for this difficult-to-treat clinical problem (Fig. 1). The planned trial will address an evidence-practice gap in the use of cannabinoid to meet a pressing need for services, the community and families, which has been identified as a priority research area by adults with neurodevelopmental disabilities, family members and clinicians in an Ontario-wide priority setting exercise (rb.gy/thr2od).

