After V 0, eligible participants will receive open-label nabilone starting with a dosage of 0.25 mg before sleep. During the dose titration phase (which could last up to 15 days), nabilone will be titrated in 0.25 mg increments every two days (with the dosing schedule "twice daily") after consultation with the study team during regular phone calls. This proposed up-titration schedule was decided based on a clinical trial of using Nabilone to treat non-motor symptoms in adults with Parkinson's disease (30). These regular phone calls will be carried out every two days during the whole dose titration phase until the participant reaches a stable dose for the open-label phase. The study team will also check whether the participants show any physical or mental changes which are believed to be attributed to AEs (based on the UKU side effect rating scale), and advise the participant and their caregivers on the next step of titration accordingly. Dose adjustments are

performed until the participant reaches the maximum permitted dose of 1 mg twice daily or experience intolerable AEs believed to be related to nabilone. If intolerable, the participant will use nabilone at the previous lower dose, entering the open label phase. Note that the suggested maximum nabilone daily dose per the product monograph is 6 mg. However, considering the vulnerability of the current target population, we choose to administer 2 mg/day at most in the current proposal following the maximum dose used in clinical trials in people with dementia (27) and Parkinson's disease (30). Moreover, nabilone is a THC analog; THC appears to reduce anxiety at low doses but becomes anxiogenic at high doses. Thus, administering nabilone at lower doses is theoretically consistent with the treatment objective for SBP.

Participants will be then on a stable, optimized nabilone dosage for four weeks, and then the trial ends with an on-site termination visit (V1). During the open-label trial phase, the study team will call the participant and their caregivers once weekly to perform a basic check-up, and to follow up with any questions or concerns from the trial processes. If there are any changes suspected to be associated with AEs, the UKU side effect rating scale will be assessed during the telephone check-up.

At V 1, the following post-treatment assessments will be completed:

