## **7. STOPPING OF THE STUDY**

### **7.1. Termination of the entire study**

Reasons for withdrawing individual participants from the study may include one or more of the following:

- a) Failure to continue to meet the inclusion criteria.
- b) Changes in participants' behaviours or situations, which meet the exclusion criteria. For example, participants become pregnant, newly use other cannabinoids, or newly use illegal psychomimetic substances as specified in Section 3.3, after the start of the trial.
- c) Major protocol violation.
- d) Participant lost to follow-up.
- e) Withdrawal of consent: Participation in the study is voluntary, and the participant can refuse or stop participation at any time. The participant's refusal to participate or withdraw from the study will not interfere in any way with the relationship with his/her doctor or hospital.
- f) Inability to tolerate the study medication or procedure.
- g) Serious adverse effects related to the study medication.
- h) New information shows that the study intervention is no longer in the participant's best interest.

In addition to these discontinuation criteria, any participant may be discontinued from the study at the discretion of the investigators if this is deemed to be in the best interest of the participant. The decision may be made either to protect the participant's health and safety, or because it is part of the research plan that people who develop certain conditions may not continue to participate. To ensure safety, we will arrange a Safety Follow-up visit, which is the same as the one for those who fully complete the trials, for participants withdrawn from the study.

Any research information recorded for, or resulting from, participation in this research study prior to the date that the participant formally withdraws from the study will be retained and may

continue to be used and disclosed by the investigators for research purposes. However, no new data will be further collected. There is no exception to the Safety Follow-up visit.

As the purpose of this phase I study is to investigate the tolerability of nabilone in adults with IDD, we will not recruit any new participants to replace the ones who withdraw from the entire trial.

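### Protocol completion, the only numerical tolerability criterion, ignores intolerance managed by a dose step-back and counts non-drug withdrawals as failures

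*Protocol*

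**What the plan says.** The primary objective in section 2 of the protocol covers both tolerability and safety. Hypothesis 1 is the part labelled tolerability: "To evaluate tolerability, we hypothesize that 80% of participants will complete the study protocol". It does not distinguish reasons for not completing. Hypothesis 2 is introduced as the safety evaluation. It also says that nabilone will be tolerated, "as quantified by lower rates of AEs than those reported in the literature of antipsychotics in IDD", but gives no numerical threshold.

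Section 3.1 sets the end of up-titration at the maximum permitted dose or at the point where participants "experience intolerable AEs believed to be related to nabilone". It then says: "If intolerable, the participant will use nabilone at the previous lower dose, entering the open label phase". It also places everyone who enters titration in the description of safety and tolerability.

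Section 7.1 lists reasons for withdrawing a participant. Some point to the drug, such as serious adverse effects related to it. One combines drug and procedures: "Inability to tolerate the study medication or procedure". Others need have nothing to do with the drug: "Participant lost to follow-up"; "Withdrawal of consent: Participation in the study is voluntary, and the participant can refuse or stop participation at any time"; major protocol violation; and newly meeting an exclusion criterion, for example where "participants become pregnant, newly use other cannabinoids, or newly use illegal psychomimetic substances". Withdrawn participants are not replaced.

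Section 8 plans for 40 participants entering titration and describes AEs by percentages. Section 12 has the principal investigator judge each AE's relationship to the drug or to study procedures, and the AE log records any action taken.

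**The concern.** Completion and tolerability separate in two directions here.

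- **Intolerance that leaves no trace in the criterion.** The step-back is the protocol's stated route for intolerable AEs during titration. Someone who takes it has been judged unable to tolerate a dose because of nabilone, yet counts towards the 80% if they finish.
- **Failures that are not intolerance.** A participant who moves away, withdraws consent or starts another cannabinoid lowers the completion rate even if nabilone caused no difficulty.

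Sections 1.1 and 2 say the results will inform a placebo-controlled pilot trial. Its planners need to know how many participants stopped because of the drug and how many could not go up in dose because of it. The Hypothesis 1 figure gives neither.

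**Working it through.** **Inputs**

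- Criterion: 80% complete (section 2, Hypothesis 1).
- Denominator: all who enter titration (3.1), planned at 40 (section 8), with no replacement (7.1).
- Intolerance in titration: step back and enter the open-label phase (3.1).
- Non-drug withdrawals: not completers (7.1).

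**The plan's own figures.** Section 8 gives no calculation for the 80%. Its one calculation, d = 0.53 with N = 30, serves the exploratory objective. It reproduces: a two-sided paired t-test at 0.05 with 29 degrees of freedom and 80% power gives d = 0.529, and power at d = 0.53 is 0.801. It has no bearing on Hypothesis 1.

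**What the criterion requires.** No test is stated, so I read it as an observed proportion of at least 80%: 0.80 × 40 = 32 completers. An observed 32/40 has an exact (Clopper-Pearson) 95% CI of 64% to 91%.

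**Direction 1: dose-limiting intolerance among completers.** Fix completers at 32 and let an assumed share s of them have had titration limited by intolerable AEs. Completers without dose-limiting intolerance number 32 × (1 − s).

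| Assumed s | Dose-limited completers | Completed without dose-limiting AEs | Hypothesis 1 reads |
|---|---|---|---|
| 0% | 0 | 32/40 = 80% | 80% |
| 25% | 8 | 24/40 = 60% | 80% |
| 50% | 16 | 16/40 = 40% | 80% |
| 75% | 24 | 8/40 = 20% | 80% |
| 100% | 32 | 0/40 = 0% | 80% |

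**Direction 2: non-drug drop-out alone.** Suppose nobody leaves because of nabilone and each participant leaves for another reason with assumed probability q, independently. The number completing, X, is then binomial(40, 1 − q), and

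P(X ≥ 32) = Σ from k = 32 to 40 of C(40, k) (1 − q)^k q^(40 − k).

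| Assumed q | P(at least 32 of 40 complete) |
|---|---|
| 5% | 1.00 |
| 10% | 0.98 |
| 15% | 0.86 |
| 20% | 0.59 |
| 25% | 0.30 |

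In counts, nine non-drug withdrawals leave 31/40 = 77.5%, and Hypothesis 1 is missed with no intolerance at all.

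The values of s and q are assumptions. Section 8 does assume 25% attrition before the open-label phase, but without giving reasons, so it is no estimate of q. That 25% would leave 30/40 = 75%, below the hypothesised 80%. This is a separate inconsistency and the present point does not depend on it.

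**The case against.** The strongest reply has four parts.

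1. **Completion is not the whole evidence.** A reader might infer that tolerability is judged by completion and nothing else. The protocol does not support that. Hypothesis 2 also speaks of being tolerated, and section 8 reports the percentage of each adverse effect, so a drug that troubled half the participants should show in the AE results. This stands. However, Hypothesis 2 has no threshold, and AE percentages do not say how many participants had titration limited.

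2. **Some intolerance already counts.** A reader might also infer that all dose-limiting intolerance is scored as success. It is not: withdrawal under 7.1 for inability to tolerate the medication, or for serious related effects, is non-completion. Only intolerance managed by the step-back escapes. With individual titration, finishing four weeks at one's own tolerated dose is a defensible meaning of tolerability. Even so, that reading needs the dose distribution beside it, and it does nothing about non-drug withdrawals.

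3. **The records may separate the causes.** It is tempting to say that the combined reason in 7.1(f) makes drug and procedure inseparable. That is not shown. Section 7.1 is a list of possible reasons and is not presented as a coding scheme. Section 12 requires a causality judgement against drug or procedures, and 7.2 lets participants skip the cognitive battery and stay in. The combined wording is therefore a minor matter.

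4. **Detail belongs in the statistical analysis plan, and little hangs on 80%.** Analysis detail may well be in a plan not at hand, and its absence is not held against the protocol. The trial is a pre-pilot with no go/no-go rule tied to 80%, so it would be too strong to say the next trial must be misled. What remains is that the protocol itself fixes the primary tolerability hypothesis on a measure that mixes causes.

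**Conclusion.** The point holds in limited form. Completion is the only numerically specified tolerability criterion. It does not respond to intolerance handled by the step-back, and it is lowered by withdrawals that need have nothing to do with nabilone. At 32/40, the share completing without dose-limiting AEs could lie anywhere from 0% to 80% with Hypothesis 1 unchanged. With no drug-related withdrawal, the chance of meeting it falls from about 0.98 to 0.30 as assumed non-drug drop-out rises from 10% to 25%.

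These sizes rest on assumed rates, on 40 participants as the denominator, on reading 80% as an observed proportion and, for the probabilities, on independent drop-out. The mechanism rests on the protocol's text alone. This is a weakness in how the endpoint is defined, not a miscalculation. It should be corrected, but it does not stop the trial from running.

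**What to change.** Reword Hypothesis 1 so that 80% completion is a feasibility figure. Base the tolerability conclusion, among all who start titration, on:

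1. the proportion who discontinue for nabilone-related AEs, using the causality assessment already made under section 12; and
2. the proportion whose up-titration was limited by intolerable nabilone-related AEs, with the distribution of final dose.

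Give each proportion an exact 95% CI. Precision will be modest: 20/40, for instance, would have an interval of 34% to 66%. As a minor aid, split 7.1(f) into intolerance of medication and intolerance of procedures.

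The cost is the rewording, one extra withdrawal reason and slightly more analysis. The titration calls, drug diary and AE log already supply the data, so no further participants or visits are needed and no dosing rule changes. The tolerability result may look less favourable than a completion rate would.

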#### Other measures

1. Demographic questionnaire
2. Current and Concomitant medications (including type, dose, and duration of treatment)\*
3. Height
4. Weight
5. Vital signs (blood pressure, heart rate, and temperature)
6. Drug diary to evaluate compliance

---

\*The high dose of benzodiazepine (more than the benzodiazepine equivalent to lorazepam 2 mg daily) and other cannabinoids, which are still used 4 weeks before the start of the use of the study drug (titration phase), are not permitted. Other concurrent medications and non-medication treatments (including behavioural therapy, psychological therapy, occupational therapy, support group etc.) are permitted before and during the trial.

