## **9.3. From nabilone**

Nabilone is indicated for severe nausea and vomiting associated with cancer chemotherapy and commercially available in Canada. Its use is usually safe and well tolerated, with sedation (~20%) and dry mouth (~10%) being the most commonly reported adverse events (no side effects of appetite and movement) in elderly with dementia or Parkinson's disease, or people with cancer (26-28, 30, 34). This safety profile is comparable to those reported in studies of CBD (36) and clonidine (37) (one of the medications for SBP of people with developmental disabilities) use in people with IDD, and less substantial relative to antipsychotics.

The addictive potential of nabilone is very low and unlikely (38), for its effect of less euphoria, slower onset of action, and more difficult titration compared to smoking cannabis. Nabilone has been shown to help with sustained abstinence from marijuana (39). The incidence of nabilone

induced full-blown psychotic disorder are also rare, and this propensity is only concerning in people with a personal or family history of schizophrenia, who will be excluded from this study. Although promising, no data ever showing efficacy and safety regarding nabilone in this population have been noted.

Per the product monograph and previous reports issued by the Canadian Agency for Drugs and Technologies in Health (26-28, 30, 34, 35), risks and side effects related to nabilone we are studying include:

- Drowsiness (66.0%)
- Vertigo (58.8%)
- Psychological high (38.8%)
- Dry mouth (21.6%)
- Depression (14.0%)
- Ataxia (reduced body coordination) (12.8%)
- Blurred vision (12.8%)
- Sensation disturbance (12.4%)
- Anorexia (loss of appetite) (7.6%)
- Asthenia (feeling of numbness and tingling) (7.6%)
- Headache (7.2%)
- Orthostatic hypotension (feeling dizzy when standing up) (5.2%)
- Euphoria (4.0%)
- Hallucinations (2.0%).

However, these estimates are influenced by factors such as drug dose, patient characteristics, detection technique, setting, and physician judgments, among others. Consequently, the side effects listed above are presented solely to indicate the relative frequency of adverse events reported in representative controlled clinical studies conducted to evaluate the safety and efficacy of nabilone across different situations.

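### Primary Hypothesis 2 judges nabilone's safety against an antipsychotic rate that the protocol never fixes, and the uncontrolled design with continuing antipsychotics cannot support that comparison

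*Protocol*

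**What the plan says.** Hypothesis 2 appears twice under the primary aim. Section 1.1 says safety will be judged "as quantified by lower rates of adverse events (AEs) and serious adverse events (SAEs) than those reported in the literature of antipsychotics in IDD". Section 2 says "as quantified by lower rates of AEs than those reported in the literature of antipsychotics in IDD", leaving out SAEs.

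Section 8 says the 40 participants entering titration are there to test Hypotheses 1 and 2. The only analysis it gives for safety is the percentage with each adverse effect. Section 3.1 calls this a description of everyone who enters titration.

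Antipsychotics are not on the excluded-drug list in Section 3.3; only a psychotropic change within 4 weeks before study drug excludes. After ruling out high-dose benzodiazepines and other cannabinoids, the footnote in Section 3.4 (Other measures) says: "Other concurrent medications and non-medication treatments (including behavioural therapy, psychological therapy, occupational therapy, support group etc.) are permitted before and during the trial".

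Table 1 schedules the UKU side effect scale from titration onward. It is not listed at screening or at V 0, nor among the screening and baseline assessments in Section 3.2.

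The only sources given for antipsychotic rates are in Section 1.4, where nabilone is called "substantially more favourable than what has been reported for antipsychotics (9, 11, 12"). No rate is quoted there.

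**The concern.** A hypothesis that is met when one rate is lower than another needs the second rate. Here it is missing, together with the event, its severity, the time window and the rule for calling a rate lower. The trial is open-label, and Section 11 has the principal investigator review accrued data and adverse events weekly. A benchmark chosen at reporting would therefore be chosen with the results known.

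The second difficulty remains even if a number is supplied. Participants may be taking antipsychotics while their adverse events are compared with rates on antipsychotics. Without a comparator arm or a pre-treatment reading on the same scale, a difference from published rates cannot be attributed to nabilone. At stake is a comparative safety statement from a first study in this population, meant to inform a series of randomised trials.

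**Working it through.** **The plan's own figure.** The only computed quantity in Section 8 is for the exploratory objective: d = 0.53 with N = 30 (40 × 0.75), paired t-test, two-sided α = 0.05, power 0.80. With the noncentral t on 29 degrees of freedom, power at d = 0.53 is 0.801 and the smallest detectable d is 0.529, so it reproduces. No corresponding figure exists for Hypothesis 2; N = 40 is justified only as a customary Phase I size.

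**Dependence on the benchmark.** Inputs: n = 40 (Section 8). The benchmark is an assumption, because the protocol gives none. The exact (Clopper-Pearson) 95% limits for x of n are the 2.5% point of Beta(x, n − x + 1) and the 97.5% point of Beta(x + 1, n − x). For x = 16 these are Beta(16, 25) and Beta(17, 24), giving 24.9% and 56.7%.

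- Against an assumed 50%: 40% < 50%, so lower.
- Against an assumed 30%: 40% > 30%, so not lower.
- If the upper limit must clear the benchmark: 56.7% > 50%, so not lower even against 50%.

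The same result changes verdict with the benchmark and also with the rule.

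**Range.** The table shows, for one event, the chance that the observed percentage falls below the benchmark, from the binomial with n = 40. The true rates of 20% and 66% are illustrations only. The last column is the largest count whose upper 95% limit lies below the benchmark.

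| Assumed benchmark | Chance of lower, true rate 20% | Chance of lower, true rate 66% | Most events allowed under the upper-limit rule |
|---|---|---|---|
| 20% | 44% | about 0% | 2/40 |
| 30% | 91% | about 0% | 6/40 |
| 40% | 99.7% | about 0% | 9/40 |
| 50% | about 100% | 1% | 13/40 |
| 60% | about 100% | 17% | 17/40 |
| 70% | about 100% | 64% | 21/40 |
| 80% | about 100% | 96% | 26/40 |

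With a true rate of 66%, moving the benchmark from 50% to 80% takes the chance of a favourable verdict from 1% to 96%, with nothing about the drug changed.

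**SAEs.** With 0/40 the upper limit is 1 − 0.025^(1/40) = 8.8%. Even with no SAE, the interval could not show a rate below any benchmark under 8.8%.

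**Like for like.** Section 1.2 puts use of antipsychotics and other psychotropics together at up to 70% of adults with IDD. That is not an antipsychotic-only figure, but it makes background antipsychotic use likely. Side effects already present at entry have no UKU reading to be subtracted from later ones. This would mostly raise the observed rate, and by an unknown amount.

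**Section 9.3, set side by side.** One paragraph describes nabilone "with sedation (~20%) and dry mouth (~10%) being the most commonly reported adverse events (no side effects of appetite and movement") and cites references 26-28, 30 and 34. The list that follows cites the same references plus 35, the product monograph. It gives drowsiness 66.0%, dry mouth 21.6%, ataxia 12.8% and anorexia 7.6%. The statement on appetite and movement conflicts directly with the last two.

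**The case against.** The strongest reply is that this is a pre-pilot whose stated purpose is preliminary data. The planned analysis is descriptive, and no test, go/no-go or stopping decision depends on Hypothesis 2. Exact intervals and AE definitions are ordinary SAP content, and the SAP is not shown. That lowers the severity: no planned analysis is invalidated. It does not remove the point, because the protocol itself sets the comparative criterion, says the sample is there to test it, and fixes the medication rules and the assessment schedule.

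There are also safeguards. The investigator judges each AE's relationship to study drug, the AE log holds start dates (Section 12), concomitant medication is recorded throughout, and psychotropics must have been unchanged for 4 weeks. These help attribution but do not isolate nabilone.

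Several stronger readings are tempting and not supported:

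- That continuing antipsychotics would help the hypothesis succeed. Background events would mostly count against it; the trouble is interpretation, not a favourable bias.
- That the two nabilone profiles allow the verdict to be chosen. Hypothesis 2 compares observed rates with antipsychotic literature, and expected nabilone rates are not part of it.
- That all of Section 9.3 is incompatible. The lower sedation and dry mouth figures are attributed to dementia, Parkinson's disease or cancer, and the text warns that estimates vary with dose, patients and detection. Only the appetite and movement statement clearly conflicts.
- That the missing SAEs in Section 2 show a changed endpoint. The Table 1 key defines AE to include severe adverse events and Section 12 covers both; this is largely wording.
- That references 9, 11 and 12 supply the benchmark. By title they are a selective review of psychotropic use, a cohort study of movement side effects and a meta-analysis of metabolic syndrome. Nothing here shows that they hold usable rates, and they are not tied to Hypothesis 2.

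**Conclusion.** The point stands, as something that should be fixed. As written, Hypothesis 2 has no determinate verdict: 16/40 meets it against an assumed 50% and fails it against an assumed 30%. A named benchmark would settle the arithmetic but not the inference. In a single arm with antipsychotics continuing and no pre-treatment UKU, the data cannot support a claim about nabilone relative to antipsychotics.

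This rests on the protocol's n = 40 and on assumed benchmarks and true rates used only to show sensitivity. How many participants will be on antipsychotics, and by how much that raises the observed rate, cannot be derived from the protocol. The Section 9.3 discrepancy is a separate correction. It weakens the stated expectation of a favourable profile but does not enter the Hypothesis 2 criterion.

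**What to change.** Restate Hypothesis 2 as an estimate. Report the percentages of participants with AEs and with SAEs that start or worsen after the first dose, using the AE log start dates, with exact 95% intervals, overall and by concomitant antipsychotic use. Draw no comparative conclusion against antipsychotics. Use the same AE/SAE wording in Sections 1.1 and 2. Adding a UKU at V 0 would be a useful extra, since worsening needs a baseline; Section 3.4 puts the scale at about 20 minutes.

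If a benchmark is kept, write the event, source and numeric rate into the protocol before any data are reviewed. Call a rate lower only if its upper 95% limit is below the benchmark, and label the result an external, descriptive comparison.

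Separately, reconcile Section 9.3. Resolve the appetite and movement statement against anorexia 7.6% and ataxia 12.8%, and explain sedation of about 20% and dry mouth of about 10% beside drowsiness 66.0% and dry mouth 21.6%.

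The cost is protocol wording and one stratified table from data already planned, with wider intervals within each subgroup. The main price is a weaker claim against antipsychotics.
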